### 5.1.2 Statistical analysis plan

The primary hypothesis will be tested solely on determined mean latencies and separately from additional, secondary and exploratory analyzes. For the primary hypothesis, we will employ a mixed model ANOVA or generalized linear mixed model. All analyzes will be considered significant when p<0.05.

All secondary variables will be analyzed post-hoc for hypothesis-generation rather than formal testing. Collected secondary parameters will be analyzed *post hoc* individually with respect to the experimental condition (D/M) and the participants state (CPAP-treatment or withdrawal). If group-level differences exist we will conduct multiple comparison tests. Time-course-effects of, for example, SDLP are intended to be analyzed using repeated measures-ANOVA between 10 4-min-long modules comprising the test drive or using paired t-tests of the first and last driven module. Integrated Driving Scores (IDS, Z-scores) will be calculated after logistic regression of driving parameters.

For secondary parameter-based models, we will first use linear mixed models and stepwise testing will be based on biological/plausibility justification rather than purely statistical significance.

Akaike Information Criterion (AIC) and k-fold cross-validation will be used to for prediction models of sleep onset/sleep accidents on the level of individual 40-min-long runs, 4-min-long modules or shorter time units to be explored. For exploring more complex models and potentially prediction models, we will include multiple secondary variables. Rather than on the determination of the averaged latency over 4 runs within a test, such analyzes will be performed per each 40-min-long run (N_run_= 4 x 54 = 216), per 4-min-long module (N_Module_ = 2160) or as running time-series-analysis in shorter time units to be explored, embracing an EPV = 10-15 (observations per predictor variable). Here we plan to test predicting sleep onset and/or sleep accident based on the selected variables within a run. We will employ Akaike Information Criterion (AIC) or AICc for small sample sizes (18): AIC-based model selection helps prevent overfitting by identifying the most parsimonious model rather than selecting significant variables arbitrarily. Cross-Validation techniques (e.g., k-fold cross-validation) will be implemented to ensure robustness and avoid overfitting. Although this approach does not rely on p-values from multiple tests but penalizes model complexity and avoids spurious associations, we still might use False discovery rate (FDR) approaches to help adjusting for false positives while maintaining statistical power. In this context Bonferroni Corrections will be too conservative and could lead to excessive type II errors (false negatives) rather than avoiding and adjusting for type I errors (false positives).

Significant findings from exploratory analyzes will be interpreted cautiously and will most likely require independent validation in future studies.

We cannot reliably aim at uncovering gender differences, but will include sex or gender in any model for control.

The statistical software R, Python, and GraphPad Prism will be used.

Any deviation from the original statistical plan will be described and justified in the final trial report. We intend to complete the study with N_total_ = 54, except recruitment success is (deemed) prohibitive within the projected study duration (LPLV 30/04/2027, see section 4.3) and possible extension of the study duration.

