Each driving simulation-based maintenance of wakefulness test (D) or maintenance of wakefulness test (M) in visits 3,4,6, and 7 comprises four 40-min-long sessions (also termed “runs”) with EEG-measurements including video, starting at 9 a.m. 11 a.m. 1 p.m. and 3 p.m.. Prior to each session, participants are asked to indicate their subjective level of sleepiness using the Karolinska Sleepiness Scale 8KSS). In each session, participants are asked to stay awake in a dark environment, either sitting still with open eyes without activation (M) or sitting still in a monotonous night-time car-following task in a driving simulator (D). Each driving simulation-based maintenance of wakefulness tests (D) includes eye tracking. Eye tracking will be included in maintenance of wakefulness tests (M), depending on availability of the instrument. Each session is followed by sample taking (blood, saliva, exhaled breath, dried blood spot). EEG-Electrodes are removed after visits 4 and 7, but checked throughout visits 3, 4, 6 and 7. An optional interview after the study phase is possible, if the patients wish to elaborate on the feedback, late effects, lessons learned, or the daily life effects they encountered after completion of all 7 study visits. Visit 1 requires an estimated presence of 1 hour. Visit 2 and 4 require an estimated presence of 1 hour. Visit 3, 4, 6, and 7 each require an estimated presence of 8 hours, with actual test durations of approximately 4 hours, i.e. four times 40-min log runs and 15 min-long sample taking.

[figure not shown]

**Figure 2.** Overall randomization scheme for the intervention group and the comparison group. W_first_ = Group starting with the sequence in the condition “withdrawal”, i.e. the intervention. C_first_ = Group starting with the sequence in the condition “continuation”. D = driving simulation-based maintenance of wakefulness test, M = maintenance of wakefulness test.

**Table 1.** Overall overview of the visits. Timing between visits 1 and 2 as well as 4 and 5 will have to be ≥ 7 days but can vary, visits 2-4 and 5-7 will have to take place on subsequent days (see also Figure 1).

| **Visit** | **0** | **1** | **2** | **3** | **4** | **5** | **6** | **7** |
| --- | --- | --- | --- | --- | --- | --- | --- | --- |
|  | **pre-study phase** | | **phase I** | | | **phase II** | | |

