## 5.2 Feature description

*Test-Latency:*

Mean MWT- or DS-MWT-latencies are determined by averaging latencies from four max. 40 min test- sessions determined by AASM-criteria (REF,) and previously reported additional/complementary parameters (e.g., sleep accidents with closed eyes, (1)) for the two tests, respectively.

*Driving Parameters*

We will collect multiple driving parameters, such as the standard deviation of lane position, SDLP, the standard deviation of velocity, SDS, number of lane departures, and LD. Collected parameters will also be used as one criterion to determine the sleep-accident-derived latency for the DS-MWT. IDS

*ET Features*

A recent review showed that eye movement features and the sleep-wake predictor model could be used to predict sleepiness (6). For example, the blink rate increases with increased sleep pressure and can be used to assess drowsiness or sleepiness. Other valuable ET metrics (5) for our setting are the saccade latency, saccade peak velocity and smooth pursuit velocity gain, which could also reflect levels of sleep deprivation and extreme sleepiness.

*EEG Features*

EEG recordings are required to determine MWT-latencies, based on precise identification of sleep onset (SO). According to AASM classification, sleep onset is defined as the start of the first epoch scored as any stage other than stage W. In most individuals this will usually be the first epoch of stage N1, characterized by SEM (slow eye movements) and LAMF (low-amplitude, mixed-frequency) in EEG activity. Electrophysiological data collected during both classical MWT and DS-MWT will provide useful additional insights into the sleep-wake transition. For example, microsleep episodes (MSEs), i.e., brief periods of sleep intrusion during wakefulness, may occur even before sleep onset. We will analyze manually- and automatically-detected MSEs (17).

*PSG Features*

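### The SDLP time-course methods assume complete 40-minute runs; the protocol is inconsistent on run length, and if runs end at sleep both methods can distort a withdrawal contrast

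*Protocol*

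**What the plan says.** Section 5.1.2 gives two methods for time-course effects, with SDLP as the example. The first is "Time-course-effects of, for example, SDLP are intended to be analyzed using repeated measures-ANOVA between 10 4-min-long modules comprising the test drive". The second is "or using paired t-tests of the first and last driven module". The Synopsis (Objectives) and objective O_s-2 in section 3.1 name the same pair. No rule says which of the two applies.

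On run length the protocol points both ways.

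- **Runs may end early.** Section 5.2 obtains the mean latency by "averaging latencies from four max. 40 min test- sessions", which sets an upper limit only. Section 5.1.2 speaks of the last module driven, a qualifier that is not needed if every run reaches module 10.
- **Runs are full length.** Section 4.3 says each test "comprises four 40-min-long sessions (also termed “runs". Section 5.1.2 plans prediction models "per each 40-min-long run (N_run_= 4 x 54 = 216), per 4-min-long module (N_Module_ = 2160", which is ten modules for every run.

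Section 5.2 adds that "Collected parameters will also be used as one criterion to determine the sleep-accident-derived latency for the DS-MWT". The missing-data rule in section 5.3 addresses data lost when a participant leaves the trial, and otherwise asks for all available data to be used where possible. It has no rule for modules not driven after sleep.

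**The concern.** If a run stops at sleep onset or at a sleep accident, neither method suits the data. A conventional ten-level repeated-measures ANOVA needs a value in each of the ten modules, so a run that stops in module 6 is lost. The first-versus-last test keeps that run but gives its driver six modules in which to deteriorate, while another driver has ten.

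The loss would not be random. Runs would stop because of sleepiness, which CPAP withdrawal is expected to increase, and SDLP is among the driving parameters from which the DS-MWT sleep-accident latency is partly derived. The outcome would therefore help to decide when its own measurement ends.

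At stake is any comparison of SDLP drift between withdrawal and continuation. Section 5.1.2 says that secondary parameters will be examined by CPAP state, so such a comparison is likely, although the time-course sentence does not itself name it.

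**Working it through.** **1. The protocol's module count.** 4 × 54 = 216 runs. 40 min ÷ 4 min = 10 modules per run. 216 × 10 = 2160, as stated. The figure holds only if every run is driven for all ten modules.

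**2. What each method measures if a run stops in module k.** With a constant drift of b SDLP units per module, the full-drive rise is 9b. The ANOVA uses the run only if k = 10. The first-versus-last difference has expectation b(k − 1), so it mixes drift with driving time. Take assumed drifts of 1.5 (withdrawal) and 1.0 (continuation), and a mean last module of 8.4 under continuation. The two conditions then look equal when 1.5(k − 1) = 1.0 × 7.4, that is at k ≈ 5.9 under withdrawal. Below that, the sign reverses. This simple form ignores the correlation between drift and stopping within runs.

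**3. How many runs might be incomplete.** Inputs: SD 13.5 min from section 5.1.1, and an assumed normal latency with mean m, because the protocol gives no expected DS-MWT mean. The share completing 40 min is 1 − Φ((40 − m)/13.5). The share reaching the start of module 10, at 36 min, is 1 − Φ((36 − m)/13.5).

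| Assumed mean (min) | Completes 40 min | Reaches start of module 10 |
|---|---|---|
| 20 | 7% | 12% |
| 30 | 23% | 33% |
| 35 | 36% | 47% |

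This is rough. The SD is pooled, read from a graph, taken from standard MWT data with a bounded range, and applied here to single runs.

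**4. Effect on the contrast.** A simulation with 400 replicates used 36 patients and four runs per CPAP state. All driving inputs are assumed: mean SDLP drift 1.0 unit per module under continuation and 1.5 under withdrawal, patient SD of drift 0.8, run SD 0.6, and residual SD 3. The stopping rate rises with the drift reached so far, and in all but the first row it is also higher under withdrawal. The true difference in rise is (1.5 − 1.0) × 9 = 4.5 units.

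| Stopping under withdrawal | Completed runs only | First vs last driven | Runs complete, withdrawal / continuation | Mean last module, withdrawal / continuation | Patients with a complete run in both states |
|---|---|---|---|---|---|
| Through SDLP only | 3.7 | 2.8 | 45% / 59% | 7.9 / 8.4 | 28 |
| Moderately higher | 2.1 | 0.2 | 22% / 59% | 6.3 / 8.4 | 19 |
| Much higher | 0.4 | −2.4 | 7% / 58% | 4.3 / 8.4 | 7 |
| Higher still | −1.0 | −3.6 | 3% / 59% | 3.3 / 8.4 | 3 |

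If runs that end in sleep also show a jump of 5 or 10 SDLP units in the last driven module, the first-versus-last result in the third row moves from −2.4 to −0.1 or +2.3. If all runs continue to 40 min, all ten modules exist and both methods recover the true difference.

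**The case against.** The strongest reply is that the premise is not in the protocol. No section says that a run stops at sleep. Section 4.3 describes sessions of 40 min, and the count of 2160 leaves no room for short runs. The mention of the last module driven could simply mean module 10, or could allow for a run stopped for another reason such as simulator sickness (section 7.2). This stands: early ending is an inference. What can be said firmly is that the passages disagree and that undriven modules have no rule.

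A second reply is that the methods are only intended, that complete-case deletion is nowhere stated, and that the protocol otherwise leans the right way. Section 5.1.2 names linear mixed models first for models of secondary parameters, section 5.1.1 values mixed models for handling missing values, and section 5.3 wants all available data used. This stands in part. None of these statements is applied to the time course, for which two other methods are named.

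A reader might also infer that the withdrawal effect will come out with the wrong sign. The documents do not support that. Attenuation is the usual result; reversal needs clearly more stopping under withdrawal, and a jump in SDLP at the sleep accident can offset the bias. Nor does the whole of O_s-2 rest on these tests: its link to CPAP is stated for driving parameters generally, and the time course is an addition.

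**Conclusion.** The point holds in a conditional form and is minor. The protocol contradicts itself on whether runs can be shorter than 40 min, and it assigns the time course two methods that work only if they cannot.

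If runs end at sleep, the loss of modules is informative, and the SDLP contrast between CPAP states can be attenuated, hidden or, under strong assumptions, reversed. No single size can be given, because the protocol states no SDLP values, drifts or stopping rates; the percentages and simulated differences are illustrations on assumed inputs. If runs always last 40 min, there is no bias from this source.

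Section 5.1.2 labels the secondary analyses as hypothesis-generating and calls for cautious interpretation. The primary comparison of mean latencies does not depend on them.

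**What to change.** 1. Reconcile sections 4.3, 5.1.2 and 5.2 on whether a run can end before 40 min, and state how modules after sleep are treated. If runs can end early, restate the module count, since 2160 would then be a maximum for 216 runs.
2. Replace both time-course methods with one linear mixed model on all modules actually driven: SDLP on time-on-task, CPAP state and their interaction, with random effects for participant and run. If every run proves complete, nothing is lost.
3. Drop the first-versus-last t-test, or restrict it to a common early window that nearly all runs cover and label it a sensitivity analysis. The mixed model uses partial runs but does not by itself remove all bias from informative stopping, so such a check is useful.
4. Report the number of modules driven per CPAP state, so that readers can judge how much was lost and how unevenly.

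The cost is a change of wording and slightly more analysis work. No new data are needed.

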## 4.3 Study procedures

The planned overall duration of the study is 24 months, with 01/05/2025 being First-Participant-in (FPFV, anticipated date of the screening/enrolment of the first patient) and 30/04/2027 being Last-Participant-Out (LPLV, anticipated date of the last participant’s final visit. A published manuscript or submission of the final report will be handed in by 30/04/2028.

Figures 1 and 2 as well as Tables 1 and 2 summarize all relevant procedures and study visits.

[figure not shown]

**Figure 1.** Overall course of the study. V = visit, PSG = @home-polysomnography, D = driving simulation-based maintenance of wakefulness test, M = maintenance of wakefulness test. Visit 1 comprises inclusion and a brief screening. Visit 2 and Visit 5 serve merely to mount PSGs.

Visit 1 comprises discussion and signing of the informed consent, inclusion, a brief screening drive to control for screening-based exclusion and the randomization lottery. In visit 2 and visit 5 the EEG-electrodes for @home-PSGs are mounted. PSGs are recorded overnight between visits 2-3, 3-4 and 5-6, 6-7 each. During visit 3, 4, 6 and 7 driving simulation-based maintenance of wakefulness tests (D) or maintenance of wakefulness tests (M) will be performed according to the respective study group, i.e. the randomized allocation of starting condition or sequence, respectively (see Figure 2). Randomization will be achieved by lottery during visit 1. Participants are invited to give feedback after the study (optionally personal or online).

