### 5.1.1 Sample size calculation

The total sample size is N_total_ = 54, consisting of the intervention group N_I_ = 36 and a healthy comparison group N_H_ = 18. (see Figure 2)

Sample sizes N_I_ = 36 for the intervention group were estimated according to formula I considering the randomized crossover RCT study design of a cohort of OSA-patients randomized both to CPAP starting condition and measurement sequence resulting in 4 groups 4 (W-DM, W-MD, C-DM, C-MD, see Figure 2) in two phases and a mixed-model ANOVA analysis. Mixed-model ANOVA accounts for the fact that repeated measures form the same person are correlated, is able to handle any missing values more effectively and considers both fixes and random effects.

[figure not shown]

Formula I

adapted from (13)

- n = Required number of participants per group.
- Z_1−α/2_​ = Z-value corresponding to the chosen significance level (e.g., 1.645 for α = 0.1 two-sided) (14).
- Z_1−β_ = Z-value corresponding to the desired power, 1.28 for 90% power) (14).
- σ = Standard deviation of the measurements = 13.5 minutes (from Bonnet & Arand) (15)
- ρ = Intra-class correlation (ICC) or correlation between repeated measures within the same participant.
- Δ = Equivalence margin or effect size = 1 pooled SD = 13.5 minutes (from Bonnet & Arand) (15)

For the sample size calculations, we use a two-sided α = 0.1 assuming that a potential difference between M and D would have a clear direction and a maximal value (bounded test range) of 40 min for the test latency. When conducting an equivalence test, using a 0.1 two-sided alpha-level effectively matches the 0.05 significance level for each side of the distribution (one for each tail), aligning the rigor of the test with the traditional hypothesis test for no difference. This assumption holds, as the reference standard deviation of 13.5 min was obtained with an equivalently bounded test range. We employ a graphically extracted and pooled standard deviation form Bonnet & Arand (15) (Figure 2 baseline and wake, p 388), the only close-to test-retest data on MWTs available.

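### The exploratory prediction models in 5.1.2 rest on a run count that omits most test days and on a predictor budget set by observations although the outcome is an event

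*Protocol*

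**What the plan says.** Protocol 5.1.2 plans models that predict sleep onset or sleep accident within a run and gives their numbers of observations: "such analyzes will be performed per each 40-min-long run (N_run_= 4 x 54 = 216), per 4-min-long module (N_Module_ = 2160". Shorter time units are left open. The predictor budget is set by "embracing an EPV = 10-15 (observations per predictor variable". Protection against overfitting comes from AIC or AICc and from cross-validation: "Cross-Validation techniques (e.g., k-fold cross-validation) will be implemented to ensure robustness and avoid overfitting".

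Section 4.3 gives the schedule: "During visit 3, 4, 6 and 7 driving simulation-based maintenance of wakefulness tests (D) or maintenance of wakefulness tests (M) will be performed". Each of these tests "comprises four 40-min-long sessions". The sample in 5.1.1 is 54, "consisting of the intervention group N_I_ = 36 and a healthy comparison group N_H_ = 18".

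The number of test days for the healthy group is not consistent. The synopsis (Study Design) has every participant attend visits 1 to 7, whereas 5.1.1 sizes that group as a crossover with no retest.

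Section 5.2 treats 40 minutes as the maximum length of a session. On driving parameters it adds: "Collected parameters will also be used as one criterion to determine the sleep-accident-derived latency for the DS-MWT".

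**The concern.** Four runs per test day multiplied by 54 people counts a single test day each, but the schedule has four test visits. The stated number therefore does not describe the data that will exist, and the module count is built on it.

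EPV ordinarily stands for events per variable. The protocol spells it out as observations per predictor while the thing predicted is an event. Under that definition the number of predictors can be raised by slicing the same recordings more finely. No participant, run or sleep onset is added. The section presents its approach as guarding against overfitting, but this rule sets no effective limit at module level or below. At stake is how far an exploratory model of sleep at the wheel can be trusted in new drivers. The comparison of MWT and DS-MWT latencies is not at stake.

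**Working it through.** **Inputs from the protocol.** 36 OSA patients and 18 healthy participants (5.1.1); four test visits, four runs per visit (4.3); ten 4-minute modules per drive and 10-15 observations per predictor (5.1.2). OSA patients take the D and M pair in both phases (5.1.1), so they have two D days and two M days.

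**Reproducing the stated figures.** 4 x 54 = 216 runs and 216 x 10 = 2160 modules. The arithmetic is right for one test day per person with every run lasting the full 40 minutes.

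**Runs from the schedule.**
- OSA: 36 x 4 visits x 4 runs = 576, of which 36 x 2 x 4 = 288 are driving. The OSA driving runs alone exceed 216.
- Healthy, two test days: 18 x 2 x 4 = 144, of which 72 are driving. Total 576 + 144 = 720 (288 + 72 = 360 driving).
- Healthy, four test days: 18 x 4 x 4 = 288, of which 144 are driving. Total 864 (432 driving).
- Undercount: 720/216 = 3.3 to 864/216 = 4.0 for all runs; 360/216 = 1.7 to 432/216 = 2.0 for driving runs.
- Maximum modules: 7200 to 8640 for all runs, 3600 to 4320 for driving runs. These are ceilings because a session may be shorter than 40 minutes.

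**Predictor budget as written.**
- Run level: 216/15 = 14.4 to 216/10 = 21.6, so 14-21.
- Module level: 2160/15 = 144 to 2160/10 = 216.

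**Predictor budget by events.** A run has at most one first sleep onset, so 216 runs hold at most 216 events. The limit is again 14-21, whether the rows are runs, modules or shorter units. The protocol gives no event rate. At assumed rates for 216 runs:
- 10%: 21.6 events, 1.4-2.2 predictors
- 20%: 43.2 events, 2.9-4.3 predictors
- 30%: 64.8 events, 4.3-6.5 predictors
- 50%: 108 events, 7.2-10.8 predictors

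With the corrected 360 driving runs and an assumed 25-50% ending in sleep there are 90-180 events: 90/15 = 6 to 180/10 = 18 predictors. The rule as written would allow 3600/15 = 240 to 3600/10 = 360 at module level.

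**Does the unstated fold unit matter?** This was checked by simulation with pure-noise predictors in 54 people. The clustering values are assumptions, since the protocol gives none.
- Run level (person-level SD 1.5 on the logit scale, 14-21 predictors, 4 or 8 runs per person, predictor ICC 0.3-0.8): folds split by row give a cross-validated AUC of about 0.53-0.62. With no clustering of the outcome it stays near 0.50.
- Module level, one onset per run, 50-144 predictors: about 0.55 if the run ends at onset and just under 0.50 if all ten modules are kept.
- Folds that keep each participant together: about 0.5 in every setting.

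**The case against.** **The undercount is conservative.** This is true. A smaller count yields a smaller budget, so the miscount does not produce overfitting. The number is still wrong and still needs correcting.

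**216 could mean runs per test.** The sentence contrasts these analyses with the average over the four runs within a test. But one test day per person would leave out either the withdrawal or the continuation days of every OSA patient, and the section does not say so.

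**Nobody intends 144 predictors.** The section speaks of selected variables, AIC-based parsimony and plausibility-led choice, and it starts secondary-parameter models as linear mixed models. That is fair, and the large allowance is a ceiling. But the ceiling is the stated rule, and it grows with every finer slice. An observations rule would suit a continuous outcome; the targets named here are events.

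**The models are exploratory.** This stands. The section promises cautious interpretation and expects independent validation, which limits the importance of the point.

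**Two stronger readings go too far.** A reader might infer that the plan cross-validates by run or by module, so that noise would look strongly predictive. The protocol places the models at those levels but does not state the fold unit, and a separate SAP could settle it. Nor is the inflation large in the settings above. Stronger assumed clustering raises it (up to 0.70 at run level with outcome ICC 0.67). At module level, the large values arise when a module outcome may be positive more than once in a run, for instance when the run's result is copied to all ten modules. A reader might also infer that accidents will be predicted from the same driving data that define them. Section 5.2 makes that possible but does not say it.

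**Conclusion.** Two statements in 5.1.2 are wrong on the protocol's own text.

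- The run count is too low by a factor of 3.3-4.0 for all runs, or 1.7-2.0 for driving runs. The range depends only on whether healthy participants have two or four test days. The module count inherits the error and is a maximum in any case.
- The predictor rule counts rows for an event outcome. It raises the module-level allowance tenfold, to 144-216, where the plan's own 216 runs support at most 14-21. That ceiling needs no assumed event rate, only that each run has one first onset at most. The lower budgets depend on the assumed rates shown.

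Fold construction and overlap between predictors and outcome are risks worth closing in the same edit. They are not stated errors. The point concerns only the exploratory prediction models and leaves the primary analysis untouched.

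**What to change.** In 5.1.2:

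1. Replace 216 and 2160 with the number of runs and the maximum number of modules, by group (OSA, healthy) and by test (D, M). First reconcile the synopsis with 5.1.1 on the healthy group's test days.
2. Define EPV as first sleep onsets (or first sleep accidents) per candidate parameter. Set the maximum number of candidate parameters from that event count, with the same limit at run, module and finer resolution.
3. State that all of a participant's runs and modules stay in the same fold, because rows are nested within 54 people.
4. When driving parameters are predictors, take EEG-defined sleep onset as the outcome and use only predictor windows that end before it.

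The cost is a few sentences and a grouping argument in the code. The downside is fewer candidate predictors and possibly a lower reported accuracy. No visit, measurement or sample size changes.

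### Section 5.1.2 credits AIC selection with cross-validation with keeping out false associations, which it does not do, and on that basis leaves false-positive control optional

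*Protocol*

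**What the plan says.** Protocol section 5.1.2 plans prediction models of sleep onset or sleep accident at the level of the 40-minute run, the 4-minute module or shorter units. On the inputs it says: "For exploring more complex models and potentially prediction models, we will include multiple secondary variables". The run-level count is 4 x 54 = 216. The finer unit is "per 4-min-long module (N_Module_ = 2160"), and model size is governed by "embracing an EPV = 10-15 (observations per predictor variable"). No number of candidate variables is given.

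Selection is by AIC, or AICc for small samples, for this reason: "AIC-based model selection helps prevent overfitting by identifying the most parsimonious model rather than selecting significant variables arbitrarily". The next sentence adds the second safeguard: "Cross-Validation techniques (e.g., k-fold cross-validation) will be implemented to ensure robustness and avoid overfitting".

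The plan then says that the approach does not rest on p-values from multiple tests, that it "penalizes model complexity and avoids spurious associations, we still might use False discovery rate (FDR) approaches to help adjusting for false positives", and that Bonferroni would be too conservative. For these models, FDR is therefore possible but not committed to. The general threshold in the same section is 0.05: "All analyzes will be considered significant when p<0.05".

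**The concern.** The sentence gives a statistical reason for leaving false-positive control optional, and the reason is wrong. AIC aims at predictive fit and does not hold the chance of including an irrelevant variable at a low level. Its implicit threshold for one extra parameter is looser than the 0.05 used elsewhere in the section.

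At stake is how the output will be read. A driving, eye-tracking or EEG variable left in the final model would naturally be reported as a predictor of falling asleep at the wheel, and a reader told that the method keeps out false associations would give it too much weight. If, in addition, the selected model were cross-validated on the same data that chose it, its performance would look better than chance when nothing predicts.

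**Working it through.** **Inputs from section 5.1.2.** Criterion AIC or AICc; 216 runs and 2160 modules; 10 to 15 observations per predictor; threshold 0.05. **Assumed:** every candidate is noise, candidates are independent, rows are independent and, for the logistic simulations, 30% of runs have the event.

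**1. The plan's own counts.** 4 x 54 = 216 and 216 x 10 = 2160, as printed. The implied ceiling on predictors is 216/15 = 14.4 to 216/10 = 21.6, so about 14 to 21 at run level (144 to 216 at module level).

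**2. Error rate per predictor.** AIC = -2 log L + 2K. Adding one 1-df predictor lowers AIC when the likelihood-ratio statistic exceeds 2. For a noise predictor that statistic is approximately chi-square with 1 df, so P(chi-square > 2) = 0.157, and 0.157/0.05 = 3.1.

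AICc adds 2K(K+1)/(n-K-1). Going from K = 2 to K = 3 at n = 216, the penalty rises from 4 + 12/213 = 4.056 to 6 + 24/212 = 6.113. The threshold is then 2.057 and the probability 0.152. At n = 2160 it is 0.157. AICc therefore changes little.

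**3. At least one noise predictor kept**, 1 - (1 - p)^k:

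| Candidates k | AIC, p = 0.157 | Mean number kept | Unadjusted 0.05 |
|---|---|---|---|
| 4 | 49.6% | 0.6 | 18.5% |
| 5 | 57.5% | 0.8 | 22.6% |
| 10 | 81.9% | 1.6 | 40.1% |
| 14 | 90.9% | 2.2 | 51.2% |
| 21 | 97.3% | 3.3 | 65.9% |

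**4. Check by simulation.** With n = 216, a continuous outcome, forward and backward selection and 300 datasets per setting, AIC kept at least one noise predictor in 60-61% (k = 5), 90-93% (k = 14) and 97-98% (k = 21) of datasets. AICc did so in 53-59%, 87-92% and 97-98%. In a logistic model, AIC kept a single noise predictor 14.7% of the time. Backward AICc logistic selection kept at least one in 83 to 90% of datasets with 14 candidates and in about 98% with 21; the 83% comes from a run of only 60 datasets.

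**5. What cross-validation adds.** There are three ways to use it:

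- *To choose whether a predictor enters.* Ten-fold cross-validation kept a single noise predictor in 18.9% of datasets, so it does not control false inclusion either.
- *To assess a model already selected on all the data.* Ten-fold cross-validated AUC averaged about 0.55 to 0.59 (14 candidates) and 0.60 (21), where the truth is 0.50. It exceeded 0.60 in 26.5 to 43% and 53% of null datasets respectively. The spread at 14 candidates partly reflects whether AUC is pooled or averaged over folds.
- *With the whole selection repeated inside each fold.* Mean AUC was 0.49 to 0.50, and with 14 candidates it exceeded 0.60 in 5% of datasets. The optimism is gone.

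**6. Sensitivity.** If the 10 to 15 rule were applied to events instead of observations, a 30% event rate would give 0.3 x 216 = 64.8 events, hence 4 to 6 candidates. At least one noise variable would then be kept in 50 to 64% of datasets. Correlated candidates lower the rates in step 3. Treating a participant's four runs as independent raises them: with an assumed intraclass correlation of 0.5 in outcome and predictors, the rate per predictor is 28 to 30%. The conclusion does not rely on that.

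**The case against.** The strongest reply is that these models carry no confirmatory weight. Section 5.1.2 labels all secondary variables hypothesis-generating, promises cautious interpretation and expects independent validation. It tests the primary hypothesis on mean latencies alone. It also bases stepwise testing on biological plausibility, and section 5.2 cites prior evidence for some features, so not every candidate need be noise. Keeping a noise predictor about 16% of the time is simply how AIC operates, and optional FDR can be defended for models offered purely for prediction. All of this stands and limits the severity. None of it makes the stated property true: a plausibility filter may shorten the candidate list, but it leaves the rate for each noise variable on the list unchanged.

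Three stronger readings are tempting and are not supported:

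- *That the plan makes the claim for AIC alone.* The sentence refers to the whole approach, which includes cross-validation.
- *That 14 to 21 candidates are planned.* That is only the ceiling implied by the plan's rule. No number is given.
- *That, under the plan's rule, a trial with no effect would nearly always show cross-validated performance above chance.* The optimistic AUC arises only if selection precedes cross-validation, and the protocol does not state the order. Selection inside the folds is an equally permitted reading and may be left to a separate analysis plan. Even under the unfavourable order, AUC above 0.60 occurred in roughly a quarter to a half of null datasets.

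**Conclusion.** The point holds as a wrong justification with a practical consequence. AIC or AICc selection with cross-validation does not keep out false associations, so that claim cannot be the reason for leaving FDR optional. The firm figure is a rate of about 0.16 per 1-df noise predictor, looser than 0.05. The rates for at least one false inclusion (about 58% with 5 candidates, 91 to 97% with 14 to 21) assume independent candidates that are all noise. The optimism in AUC (about 0.55 to 0.60 instead of 0.50) further assumes a 30% event rate and selection on all data before cross-validation. Because the models are exploratory and the primary analysis is unaffected, the point is minor to moderate. It should be corrected, but it does not threaten the trial's main conclusion.

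**What to change.** In section 5.1.2:

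1. Delete the statement that the approach keeps out false associations.
2. State that the whole AIC or AICc selection is repeated inside every cross-validation fold and that performance is reported only from those folds.
3. Choose one of two rules for individual variables. Either commit to FDR control for any claim that a variable is associated with sleep onset or sleep accident, or report selected variables as prediction-only, with the frequency of their selection across folds.

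Comparing performance with a permutation null (outcomes permuted, whole selection rerun) is a useful option but not needed to correct the text. The cost is a few sentences and more computing time, with no extra participants or data. The reported performance will probably look less favourable.
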